## Abstract

**Introduction::**

There are many studies on the relationship between serum levels of hyperbilirubinemia and hearing impairment. However, the mechanism of hyperbilirubinemia on auditory impairment is not clear.

**Methods and analysis::**

A total of 1000 children with hyperbilirubinemia who are mainly indirectly elevated bilirubin in the full-term neonatal ward of Xiamen Children's Hospital from March 2020 to September 2020 will be enrolled. Using second-generation high-throughput sequencing technology, 127 deaf-related genes were sequenced from the collected samples. At the same time, physical audiometry was performed on the selected persons and audiometry data were recorded.

**Discussion::**

In this study, we will combine gene sequencing with clinical indications of hyperbilirubinemia to find the loci suitable for high-frequency pathogenic deafness related to hyperbilirubinemia, so as to provide early guidance for deafness gene screening in children with hyperbilirubinemia.

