## Introduction

1

Congenital hearing impairment is the most common congenital disease, with an incidence of about 0.1% to 0.3% in healthy newborns and as high as 2% to 4% in high-risk newborns.^[1]^ The most common risk factors for neonatal hearing loss include central infection, neonatal sepsis, hyperbilirubinemia, perinatal asphyxia and hypoxic encephalopathy, preterm delivery, low birth weight, low Apgar score, prolonged mechanical ventilation, and ototoxic agents. Children with hyperbilirubinemia whose serum total bilirubin level reached the blood exchange indicator are one of the common risk factors for hearing loss in children with Neonatal intensive care unit (NICU).^[2]^ The mechanism of hyperbilirubinemia on auditory impairment is not clear. Some scholars believe that hearing loss is a prominent manifestation of bilirubin neurotoxicity.^[3]^ The brain stem auditory pathway is particularly sensitive to the toxic effect of bilirubin.^[4,5]^ High bilirubin levels can even cause permanent damage to nerve development, mainly including deafness and infant cerebral palsy.^[6,7]^

This study protocol will explore the occurrence characteristics of hearing impairment in neonatal children with hyperbilirubinemia, the relationship between serum bilirubin level, unbound bilirubin and the occurrence of hearing impairment, the mutation characteristics of deafness gene in children with hearing impairment, and the difference between deafness gene and normal population.

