### Participants

2.3

A total of 1000 cases of neonatal hyperbilirubinemia were diagnosed in the full-term neonatal ward of Xiamen Children's Hospital from March 2020 to September 2020.

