#### Inclusion criteria

2.3.1

The inclusion criteria are as follows:

1.Newborn ≤ 28 days, gestational age > 35 weeks, weight ≥ 1.8 kg;2.Apgar score >7 points at 1 minute, 5 minutes, and 10 minutes after birth;3.Neonatal who were first diagnosis as hyperbilirubinemia, not combined with elevated bilirubinemia, will receive the physical audiometry. Hearing screening was completed within 48 hours after admission: distortion product otoacoustic emission (DPOAE) and automatic auditory brainstem response (AABR) were applicable for hearing screening.

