#### Exclusion criteria

2.3.2

The exclusion criteria are as follows:

1.Family history of deafness;2.History of birth anoxia, neonatal asphyxia;3.Plane malformation, abnormal middle ear function;4.Neonatal intracranial infection, intracranial hemorrhage, neonatal hypoxic-ischemic brain injury;5.History of cytomegalovirus infection and fever during pregnancy, history of ototoxic drugs, and mother's congenital nervous system history of disease;6.Further exclude those with incomplete clinical data.

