### Data collection

2.4

Neonatal patients (1000 cases) diagnosed with hyperbilirubinemia were selected, and 2 ml of blood was collected from the selected persons. Using second-generation high-throughput sequencing technology, 127 deaf-related genes were sequenced from the collected samples. At the same time, physical audiometry was performed on the selected persons and audiometry data were recorded. Genetic test data and physical audiometry data were correlated and analyzed to find the pathogenic loci of hyperbilirubinemia susceptibility to deafness. For those patients with definite symptoms of hyperbilirubinemia and deafness, and no pathogenic loci were detected in 127 genes, blood was collected from these patients, and total exon sequencing was performed to analyze about 22,000 genes and find new pathogenic loci.

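### The described hearing test comes after hyperbilirubinemia is diagnosed, so a locus for deafness present at birth can be reported as a locus of susceptibility to bilirubin

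*Protocol article*

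**What the plan says.** - **Who is studied.** Section 2.3 (Participants): "A total of 1000 cases of neonatal hyperbilirubinemia were diagnosed in the full-term neonatal ward". Section 2.3.1 admits infants by the criterion "Newborn ≤ 28 days, gestational age > 35 weeks, weight ≥ 1.8 kg". Those tested are described as "Neonatal who were first diagnosis as hyperbilirubinemia".
- **When hearing is tested.** Section 2.3.1: "Hearing screening was completed within 48 hours after admission", by DPOAE and AABR. Section 2.4 places audiometry at the same time as blood sampling and sequencing of the 127-gene panel.
- **Who is excluded.** Section 2.3.2 lists "Family history of deafness", asphyxia, malformation or abnormal middle ear function, intracranial disease, cytomegalovirus infection or fever in pregnancy, and ototoxic drugs, among others. The child's own congenital deafness and a failed birth screen are not listed.
- **How the result is read.** Section 2.4: "Genetic test data and physical audiometry data were correlated and analyzed to find the pathogenic loci of hyperbilirubinemia susceptibility to deafness". The Abstract gives the goal as to "find the loci suitable for high-frequency pathogenic deafness related to hyperbilirubinemia". Section 2.5 makes the audiometry result the dependent variable of the logistic regression.
- **Background rate.** The Introduction describes congenital hearing impairment "with an incidence of about 0.1% to 0.3% in healthy newborns and as high as 2% to 4% in high-risk newborns".

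**The concern.** A statement that a locus makes infants susceptible to deafness from hyperbilirubinemia needs hearing to have been intact before bilirubin rose. A single test after the diagnosis cannot show that. An infant born deaf from a recessive variant, with hearing parents and no affected relative, meets every listed criterion. If that infant becomes jaundiced, the described data look the same as those of an infant whose hearing was damaged by bilirubin.

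The choice of genes makes this more than general confounding. The panel consists of deafness genes, so an infant with genetic deafness from birth is the kind of case most likely to create a genotype-hearing association without any contribution from bilirubin. All participants have hyperbilirubinemia, so the cohort contains no unexposed infants in whom the same locus could be seen to act alone. The Introduction's comparison with the normal population concerns genes, not hearing. The article intends its loci to guide gene screening in children with hyperbilirubinemia, so a wrong label would carry over into that guidance.

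**Working it through.** The article gives no power calculation or expected case count, so there is no figure of its own to reproduce. The check has two parts.

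**1. Expected number born impaired regardless of bilirubin**

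Inputs: n = 1000 (section 2.3); p = 0.1% to 0.3%, the healthy-newborn rate (Introduction). Applying that rate to this cohort is an assumption.

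- Expected number = n × p: 1000 × 0.001 = 1; 1000 × 0.003 = 3.
- Chance of at least one = 1 − (1 − p)^n: 1 − 0.999^1000 = 0.63; 1 − 0.997^1000 = 0.95.

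The exclusions for family history, cytomegalovirus infection and malformation may lower these numbers. The article does not say by how much.

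**2. Could so few infants produce a significant locus?**

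This is an illustration, not an estimate. Assumptions: every infant born deaf carries one and the same locus; no other impaired infant carries it; the number of carriers is chosen freely; the total impaired is set at 20 or 40 (1000 × 2% and 1000 × 4%, borrowing the Introduction's high-risk rate). The test is Fisher's exact test on carrier status by hearing result, judged against the article's threshold of P < .05.

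| Born-deaf carriers | All carriers | P, 20 impaired | P, 40 impaired |
|---|---|---|---|
| 3 | 10 | 0.0008 | 0.006 |
| 3 | 20 | 0.006 | 0.042 |
| 1 | 5 | 0.10 | 0.18 |
| 1 | 10 | 0.18 | 0.34 |
| 1 | 20 | 0.34 | 0.56 |

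For example, 3 of 10 carriers impaired against 17 of 990 non-carriers gives P = 0.0008. Under these favourable assumptions, three infants born deaf are enough to put a locus with no link to bilirubin below the threshold. One infant is not.

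**The case against.** **Silence is not absence.** A reader might infer that no hearing status from before the jaundice exists, or that infants born deaf are definitely counted as bilirubin cases. The article does not say either. In section 2.3.1 the word for a first occurrence belongs to the diagnosis of hyperbilirubinemia, not to the hearing test. This is a condensed article, and a birth-screen result may be held in the full protocol or case report form. This part stands, and the point is limited accordingly. What the article does fix is the timing of the described test and the susceptibility reading of its correlation with genotype.

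**The share of cases.** A reader might divide 1 to 3 by 40 to 20 and conclude that 2.5% (1/40) to 15% (3/20) of impaired infants were born deaf. The documents do not support this. Both rates in the Introduction are for congenital impairment, so the second is not a total that contains the first. The high-risk rate covers high-risk newborns generally, while sections 2.3.1 and 2.3.2 remove many of the listed risks. No impairment rate for this cohort is given. Nor is there any figure for the share among panel-positive infants.

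**The purpose is screening guidance.** For choosing loci to screen in jaundiced newborns, an infant who was already deaf is still relevant, and section 2.1 speaks only of correlation. That justifies keeping the full-cohort analysis. It does not justify the susceptibility wording of section 2.4.

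**Other data help with attribution.** The study also relates serum and unbound bilirubin to hearing, uses multivariable regression and records two test modalities. None of these shows that hearing was normal beforehand.

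**A birth screen may come too late.** Section 3 places jaundice especially in the first week, so some screens may follow the bilirubin rise. This stands, and it argues against making a restricted subset the only analysis.

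**Conclusion.** The concern holds as a limit on what may be concluded. The described test follows the diagnosis, the exclusions leave in infants born deaf without a family history, and the article describes no earlier hearing result and no hearing test in infants without jaundice. Read as section 2.4 reads it, the genotype-hearing correlation can label an ordinary congenital-deafness locus as a bilirubin-susceptibility locus.

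The number of infants concerned is small. It rests on the healthy-newborn rate applying to this cohort and is an upper guide if the exclusions remove some of them. The significance illustration shows only that mislabelling is possible at the upper end of that range, not that it is likely. The genotype-hearing correlation itself is not invalid; what is unsupported is its causal wording.

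**What to change.** 1. Where available, abstract the newborn hearing screen result and its date, together with the timing of the bilirubin rise.
2. Classify infants who failed before the rise as having pre-existing loss and report them separately.
3. Keep the full-cohort genotype-hearing correlation. Repeat it in infants with a documented pass before the rise, and let that analysis support any susceptibility statement.
4. Treat infants with no earlier screen as having unknown prior hearing status.
5. If earlier screens cannot be obtained, restate the conclusion in the Abstract and section 2.4 as loci associated with hearing impairment among infants with hyperbilirubinemia, not susceptibility to deafness from it.

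The cost is a little record abstraction and one repeated analysis. The susceptibility statement would rest on a smaller subset, because early jaundice may precede the screen. The article does not say how many infants have an obtainable screen, so the size of that subset is unknown.

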**Trial registration::**

Chinese Clinical trial registry: ChiCTR2000030075.

## Introduction

1

Congenital hearing impairment is the most common congenital disease, with an incidence of about 0.1% to 0.3% in healthy newborns and as high as 2% to 4% in high-risk newborns.^[1]^ The most common risk factors for neonatal hearing loss include central infection, neonatal sepsis, hyperbilirubinemia, perinatal asphyxia and hypoxic encephalopathy, preterm delivery, low birth weight, low Apgar score, prolonged mechanical ventilation, and ototoxic agents. Children with hyperbilirubinemia whose serum total bilirubin level reached the blood exchange indicator are one of the common risk factors for hearing loss in children with Neonatal intensive care unit (NICU).^[2]^ The mechanism of hyperbilirubinemia on auditory impairment is not clear. Some scholars believe that hearing loss is a prominent manifestation of bilirubin neurotoxicity.^[3]^ The brain stem auditory pathway is particularly sensitive to the toxic effect of bilirubin.^[4,5]^ High bilirubin levels can even cause permanent damage to nerve development, mainly including deafness and infant cerebral palsy.^[6,7]^

This study protocol will explore the occurrence characteristics of hearing impairment in neonatal children with hyperbilirubinemia, the relationship between serum bilirubin level, unbound bilirubin and the occurrence of hearing impairment, the mutation characteristics of deafness gene in children with hearing impairment, and the difference between deafness gene and normal population.

## Methods and analysis

2

### Main aims

2.1

We aim to clarify the correlation analysis between neonatal hyperbilirubinemia and deafness gene. Flow chart of study protocol was shown in Figure 1.

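### Every enrolled infant has hyperbilirubinemia, so the main aim as worded and the normal-population comparison have no comparator, and a genotype–hearing association among cases cannot by itself identify bilirubin-susceptibility loci

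*Protocol article*

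**What the plan says.** The main aim (Protocol article, 2.1) is stated in one sentence: "We aim to clarify the correlation analysis between neonatal hyperbilirubinemia and deafness gene".

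The sample is one group throughout:
- Abstract, Methods and analysis: "A total of 1000 children with hyperbilirubinemia who are mainly indirectly elevated bilirubin".
- 2.3 Participants: "A total of 1000 cases of neonatal hyperbilirubinemia were diagnosed in the full-term neonatal ward".
- 2.3.1 Inclusion criteria, item 3: "Neonatal who were first diagnosis as hyperbilirubinemia".
- 2.4 Data collection, on who gives blood and is tested: "Neonatal patients (1000 cases) diagnosed with hyperbilirubinemia were selected".

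Section 2.3.3 defines the condition as yes or no, by a bilirubin level above an hour-specific 95th percentile.

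Two further goals go beyond description of the cases. The Introduction, repeated in the Discussion, promises "the difference between deafness gene and normal population". Section 2.4 says that genetic and audiometry data will be related in order to "find the pathogenic loci of hyperbilirubinemia susceptibility to deafness".

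Section 2.5 makes the audiometry result the dependent variable of a binary logistic regression, with variables significant in univariate analysis as predictors. It mentions comparisons between groups without defining the groups, and it mentions no interaction. Section 2.3.2 excludes infants with "Family history of deafness".

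**The concern.** An association between two variables can be estimated only if both vary in the sample. Here one of the two variables in the main aim is fixed by eligibility. The normal-population goal likewise needs a second set of genotypes, and the article neither enrols nor names one.

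The third problem matters most for the published message. A susceptibility locus is one whose effect on hearing depends on bilirubin. The stated analysis relates genotype to hearing among infants who all have high bilirubin, using a panel of 127 genes chosen because they are already linked to deafness. An ordinary deafness gene would be expected to show an association in that analysis. If it is then reported as a bilirubin-susceptibility locus, the screening guidance proposed in the Abstract would rest on a mechanism that the study did not test.

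**Working it through.** **Plan's own figure.** The sample size of 1000 is given without effect size, power or carrier rate, so there is no calculation to reproduce.

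**Step 1: main aim as a yes/no exposure.** Let H = 1 for hyperbilirubinemia. Eligibility sets H = 1 for all 1000 infants, so SD(H) = 0. The correlation cov(G, H) / [SD(G) × SD(H)] has a zero denominator. The 2 × 2 table of genotype by H has an empty column, so the odds ratio is also undefined.

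**Step 2: normal-population comparison.** Normal infants enrolled: 0. External reference datasets named: 0.

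**Step 3: what the case-only analysis can distinguish.** Among cases, the data depend only on the risk of impairment given genotype when H = 1. Take two variants, both with relative risk R among cases:
- variant A has relative risk R at normal bilirubin too (an ordinary deafness gene);
- variant B has relative risk 1 at normal bilirubin (a true susceptibility locus).

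They differ only where H = 0, and no such infant is observed. Their expected tables and rejection probabilities in the case-only test are therefore identical.

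**Step 4: how often variant A would be flagged.**

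Inputs:
- n = 1000 (2.3).
- Impairment 2–4%, the Introduction's figure for high-risk newborns. Applying it to this cohort is an assumption.
- Two-sided 0.05. Section 2.5 gives P < .05; two-sided is assumed.
- Carrier frequency f of 1–5% and R of 5 or 10, both assumed.

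With overall rate r, the non-carrier risk is p0 = r / (1 − f + fR) and the carrier risk is p1 = R × p0.

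Example with f = 3%, r = 4%, R = 5: p0 = 0.04 / (0.97 + 0.15) = 0.0357 and p1 = 0.179. That gives about 30 × 0.179 = 5.4 impaired carriers and 970 × 0.0357 = 34.6 impaired non-carriers.

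Simulated proportion with Fisher's exact P < 0.05 (1000 runs each):

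| Carrier frequency | Impairment | R = 5 | R = 10 |
|---|---|---|---|
| 1% | 2% | 23.8% | 53.5% |
| 1% | 4% | 41.5% | 82.8% |
| 3% | 2% | 50.7% | 87.6% |
| 3% | 4% | 78.1% | 99.4% |
| 5% | 2% | 66.4% | 95.7% |
| 5% | 4% | 91.5% | 99.9% |

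Monte Carlo standard error is at most √(0.25/1000) = 1.6 percentage points. By Step 3, these are equally the probabilities of flagging variant B.

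**Step 5: could an interaction separate A from B within cases?** Expected impaired infants: 1000 × 0.02 = 20 to 1000 × 0.04 = 40. Impaired carriers at R = 5:
- low end (f = 1%, r = 2%): p1 = 5 × 0.02 / 1.04 = 0.096, and 10 × 0.096 ≈ 1;
- high end (f = 5%, r = 4%): p1 = 5 × 0.04 / 1.20 = 0.167, and 50 × 0.167 ≈ 8.

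A genotype-by-bilirubin slope for a single variant would thus rest on about 1 to 8 infants, with bilirubin observed only above the diagnostic threshold.

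**The case against.** The strongest reply is that the one-sentence aim is loosely worded and the study's working questions are sound. The Introduction lists serum bilirubin level and unbound bilirubin among the factors to be studied. Both vary among cases, and an hour-specific threshold leaves further spread in absolute level. This stands. A reader might infer from the zero-variance argument that the design can estimate nothing of interest. It does not show that: frequency of impairment, level against hearing, genotype against level and genotype against hearing are all estimable among cases. For screening infants with hyperbilirubinemia, the last of these is useful even without an interaction.

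A second reply is that a normal population may mean published frequencies, and that a condensed article can leave the dataset to the full protocol. The flow chart is also not visible. This stands in part. The comparison is not impossible, but the goal is stated twice with no comparator, and every textual description of the sample is of cases only.

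A third reply is that section 2.5 lists no model terms and so does not rule out an interaction. That is fair. The point rests on section 2.4, which draws the susceptibility conclusion directly from relating genotype to audiometry.

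Finally, a reader might infer that excluding a family history of deafness seriously biases any outside comparison. The direction is plausible, but the documents give nothing from which to size it. The same exclusion also removes some ordinary hereditary deafness, which partly eases the mislabelling problem without removing it.

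**Conclusion.** The point holds in three limited parts. First, the main aim, read as presence of hyperbilirubinemia against deafness genes, cannot be estimated in this sample. Second, the normal-population comparison has no enrolled or named comparator. Third, the susceptibility conclusion does not follow from the stated analysis, because ordinary deafness genes and bilirubin-dependent ones produce the same case-only result.

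The first and third parts follow from the eligibility rule and need no assumed figure. The 24–92% and 54–99.9% ranges are illustrative. They depend on the assumed carrier frequencies and relative risks, on a 2–4% impairment rate, and on one test at 0.05.

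Two stronger readings should be avoided. It is not true that no result from this design could bear on susceptibility, since bilirubin varies among cases and an interaction can be written down. Nor would adding that interaction rescue the claim: with 20–40 impaired infants and bilirubin truncated from below, it is close to inestimable for a single variant, and a null result would not show an equal effect at normal bilirubin.

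**What to change.** 1. Restate the main aim as the association of panel genotype with hearing result among infants with hyperbilirubinemia.
2. Report hits as *deafness-associated variants in infants with hyperbilirubinemia*. Remove the susceptibility wording from section 2.4 and any matching claim in the Abstract.
3. Add one genotype-by-continuous-bilirubin interaction, with genotype taken at gene level or as carriage of any pathogenic variant. Present it as an exploratory estimate with its interval. State beforehand that it will be very imprecise and that a null result says nothing firm about normal bilirubin levels.
4. Delete the normal-population aim, or make it descriptive against one named, ancestry-matched reference with the same genes and variant classification. Note that the family-history exclusion may lower the cohort's carrier frequency by an unknown amount.

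This needs no extra infants or tests. The price is a narrower claim and one imprecise exploratory term.

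Keeping the main aim as worded would instead need a concurrent group without hyperbilirubinemia, sequenced in the same way. For scale, with assumed carrier rates of 3% and 6%, two-sided 0.05 and 80% power, that is 749 infants per group. With rates of 3% and 4.5% it is 2518 per group. That would be a different study and is not required for the changes above.
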